### Participant timeline

Participant timeline is described in Fig. 2.

**Fig. 2 Fig2:**
[figure not shown]
Schedule of enrolment, interventions, and assessments

### Sample size

This will be a randomized controlled trial, seeking to evaluate efficacy of three methods for treatment of Parkinson’s FOG. The main observation index will be gait parameters. Since there is no three-dimensional gait analysis result to evaluate the effect of music exercise therapy on Parkinson’s FOG, before this study, we will temporarily use results of the unified Parkinson’s disease assessment scale (UPDRS III) from our preliminary trial for calculations. According to the pretrial, the mean value of UPDRS (III) score reduction of three groups, after treatment, is predicted to be 20.7 ± 16.6, 7.9 ± 6.3 and 2.6 ± 2.2, respectively. We will perform a two-sided test, with *α* and assurance (test efficiency) of 0.05 and 90%, respectively. According to calculations from the Pass software method (Pass15), our sample size will be 66 cases. However, we will enroll at least 81 cases, due to a 20% drop out rate.

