**Methods/design:**

This three-arm randomized controlled trial will evaluate clinical efficacy of music exercise therapy in improving the freezing of gait in Parkinson’s patients. We will recruit a total of 81 inpatients with Parkinson’s disease, who meet the trial criteria. The patients will randomly receive music exercise with and without music as well as routine rehabilitation therapies, followed by analysis of changes in their gait and limb motor function after 4 weeks of intervention. We will first use a three-dimensional gait analysis system to evaluate changes in patients’ gait, followed by assessment of their limb function, activity of daily living and fall risk.

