### Concealment mechanism

After signing the informed consent, participants will be randomly divided into the three aforementioned groups, at a ratio of 1:1:1. We will keep the allocation hidden during randomization. Slips of paper with treatment allocation will be placed in a sequentially numbered sealed opaque envelope and then opened in turn after obtaining informed consent. The research assistant will inform participants of their assigned study arm.

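### Minor arithmetic error: enrolling 81 covers about 18.5% drop-out, not the stated 20%, if 66 evaluable patients are required; the effect on power is negligible

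*Protocol article*

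**What the plan says.** The Sample size section of the protocol article takes the pilot reductions in UPDRS III for the three groups, "20.7 ± 16.6, 7.9 ± 6.3 and 2.6 ± 2.2". It sets a two-sided test with alpha and power as "assurance (test efficiency) of 0.05 and 90%, respectively". From PASS 15 it then reports: "our sample size will be 66 cases. However, we will enroll at least 81 cases, due to a 20% drop out rate". It does not state the formula used for the drop-out allowance.

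The Methods/design paragraph of the abstract repeats the enrolment figure without the floor: "We will recruit a total of 81 inpatients". The Concealment mechanism section allocates "at a ratio of 1:1:1", so 66 means 22 per arm and 81 means 27 per arm.

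**The concern.** A drop-out allowance should leave the required number of evaluable patients after the assumed loss. Here it does not quite do so: 66, 20% and 81 cannot all be true together. The pattern fits a common slip, in which the required number is multiplied by one plus the drop-out rate when it should be divided by one minus that rate.

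The 90% power is calculated for 66 patients, and this section is the article's only justification of the trial's size. A reader who checks the sentence will find that it fails on its own figures, so the size of the discrepancy needs to be established.

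**Working it through.** **Inputs.** All are from the Sample size section except the allocation ratio, which is from Concealment mechanism.

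- Mean reductions 20.7, 7.9 and 2.6, with SDs 16.6, 6.3 and 2.2
- Two-sided alpha 0.05, power 90%
- Required total 66; drop-out 20%; enrolment 81
- Allocation 1:1:1

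**Step 1: reproduce the 66.** The test behind the PASS calculation is not named, so the models here are assumptions. Two of them return the stated figure.

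- One-way ANOVA with three equal arms and a common SD of 16.6 (the largest of the three). The mean of the means is 31.2/3 = 10.4. The squared deviations sum to 10.3² + 2.5² + 7.8² = 173.18. The noncentrality is n × 173.18/16.6² = 0.628n. The smallest n reaching 90% is 22 per arm (power 91.2%), which gives 66.
- Two-sided t test of the first group against the second. The difference is 20.7 − 7.9 = 12.8, and the variance sum is 16.6² + 6.3² = 315.25. The smallest n reaching 90% is again 22 per arm (Welch power 90.3%), and 3 × 22 = 66.

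**Step 2: reproduce the 81.** Multiplying per arm gives 22 × 1.2 = 26.4, rounded up to 27, and 3 × 27 = 81 exactly. This is an inference about how the figure arose. The discrepancy in Step 3 does not depend on it.

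**Step 3: check the allowance.**

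- Expected completers: 81 × 0.80 = 64.8, or 27 × 0.80 = 21.6 per arm
- Gap: 66 − 64.8 = 1.2 patients, which is 1.8% of 66
- Largest drop-out that keeps 66: 1 − 66/81 = 15/81 = 18.5%
- Enrolment that keeps 66 at 20% loss: 66/0.80 = 82.5, so 83; per arm 22/0.80 = 27.5, so 28, and 3 × 28 = 84

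**Step 4: effect on power at the expected number of completers.**

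| Model that reproduces 66 | 22 per arm | 21.6 per arm | Loss |
|---|---|---|---|
| ANOVA, common SD 16.6 | 91.2% | 90.6% | 0.6 point |
| Welch t test, first v second group | 90.3% | 89.7% | 0.6 point |

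Both models lose about 0.6 of a point and stay within half a point of 90% or above it.

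**The case against.** The strongest reply is that nothing of substance turns on this. Several parts of that reply stand.

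- The gap is 1.2 expected completers, and the 20% is a round planning figure with no stated source.
- The Sample size section sets 81 as a minimum, so enrolling 83 or 84 would comply with it. This mitigates the error but does not remove it, because the abstract gives 81 as the total and the sentence ties 81 to 20% drop-out.
- The power model is inferred. With the root-mean-square SD of 10.3, the same ANOVA needs only 9 per arm (27 in total). A change of 0.6 of a point is far smaller than that uncertainty.

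A reader might go further the other way and infer that the trial misses its 90% power. The documents do not support that. Under the ANOVA that reproduces 66, power at the expected 21.6 per arm is still 90.6%. It drops below 90% in that model only if 21.6 is rounded down to 21 in every arm, which means 63 completers and 18/81 = 22% drop-out, more than the protocol assumes. The Welch comparison dips 0.3 of a point below 90%, which is of no practical consequence.

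Nor does it help to argue from the chance of ending with fewer than 66 completers. A drop-out allowance targets the expected number. Even a correctly inflated total would leave a sizeable chance of falling short.

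**Conclusion.** The point holds as a minor error. The sample-size sentence is wrong as written: with 66 required, 81 covers 18.5% drop-out and not 20%, and 20% loss leaves about 65 evaluable patients. This follows from the article's own figures and needs no assumption, and no fuller protocol or analysis plan could make those three numbers agree.

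The consequence is negligible: about 0.6 of a percentage point, with power at roughly 90%. That part assumes one of the two models that reproduce 66, equal arms, and losses spread evenly over the arms. It concerns UPDRS III only, the measure on which the calculation was made, and says nothing about power for the gait outcome.

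**What to change.** Correct the sentence in the Sample size section in one of two ways:

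- at least 81 patients will be enrolled, which allows for about 18.5% drop-out; or
- 81 patients will be enrolled, of whom about 65 are expected to be evaluable at 20% drop-out.

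Either wording agrees with the total in the abstract and costs one edited sentence. No extra patients are needed. If the sponsor prefers to keep both the 20% allowance and 66 evaluable patients, the matching total is 83, or 84 with 28 per arm. The abstract would then need the same figure, at a cost of two or three more patients. Stating the inflation formula would let readers check the number.

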### Recruitment and consent

Recruitment of patients began on June 1, 2020, and will be completed on December 31, 2021, or after the required number is obtained, whichever comes first. If there are not enough participants recruited by the deadline, we will submit an application for extension of time. Participant recruitment will consist of three strategies. Firstly, advertisements will be published on Shanghai Second rehabilitation hospital’s website or other online channels. Secondly, information will be shared via posters displayed in Shanghai Second rehabilitation hospital. Thirdly, recruitment posters will be distributed in nearby communities or primary clinics. Rehabilitation physicians will be requested to provide a list of individuals who meet the aforementioned inclusion criteria, while ineligible ones will be excluded. The study coordinator will invite eligible patients for the trial, by phone. Within 2 weeks of receiving the invitation, patients will receive a telephone call from a research assistant who will provide further information and ask them whether they are interested to participate. Finally, participants who provide a written informed consent and complete the baseline assessment will be randomized into the three groups and subjected to treatments.

### Consent

All participants will be required to provide a written informed consent prior to inclusion in the study. We will prepare the informed consent form, necessary audio, pictures, and other relevant materials in advance to help the participants clearly understand the purpose of the trial before recruitment. We will also explain to the participants the benefits and potential risks of participating in this study and the relevant safety measures we have put in place during the trial.

## Randomization and allocation

### Sequence generation

Randomization will be accomplished by a trained researcher, using a randomization software (Microsoft Excel) to generate a sequence of random numbers.

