### Eligibility criteria

#### Inclusion criteria

Participants that meet the following criteria will be included in the study: (1) clinically diagnosed with Parkinson’s disease [21]; (2) brain computed tomography (CT) and other related imaging scans confirm no brain organic disease; (3) can stand for at least 30 min, with or without auxiliary equipment, and can walk independently for 3 m or more; (4) aged between 40 and 70 years; (5) clinically manifest frozen gait, with stage 2 or 3 Hoehn and Yahr; (6) respond to levodopa or other dopaminergic therapies; (7) exhibit stable condition, clear consciousness, no aphasia, and mental retardation and can understand the content of the scale and cooperate with the examination and treatment; and (8) agree to sign an informed consent form.

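### No restriction or stratification by Hoehn-Yahr stage is named for the 1:1:1 allocation, and the named tests do not adjust for stage, so a sizeable chance imbalance in severity between small arms would go uncorrected

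*Protocol article*

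**What the plan says.** Under Sequence generation, the whole stated method is that a researcher will be "using a randomization software (Microsoft Excel) to generate a sequence of random numbers". The Concealment mechanism section adds that participants will be "randomly divided into the three aforementioned groups, at a ratio of 1:1:1", and that "Slips of paper with treatment allocation will be placed in a sequentially numbered sealed opaque envelope and then opened in turn". It does not say how many slips each arm has, or whether the order is restricted.

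Under Sample size, "our sample size will be 66 cases", raised to at least 81 for drop-out. The Inclusion criteria admit patients who "clinically manifest frozen gait, with stage 2 or 3 Hoehn and Yahr". The section on analysis of primary and secondary outcomes names a *t* test, ANOVA with LSD or SNK comparisons, and a rank sum test. It names no covariate or stratification factor.

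Taken as a whole, the article neither describes a balancing method nor says that randomisation is simple or unrestricted.

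**The concern.** A 1:1:1 ratio holds exactly only if something enforces it: blocks, or a fixed count of slips per arm. A bare sequence of random numbers gives it on average. With 81 patients in three arms, an unenforced ratio will usually leave visibly unequal arms, while the sample size was worked out for equal ones.

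The second issue does not depend on arm size. Hoehn-Yahr stage is the severity grading that the trial itself uses for eligibility. With about 27 patients per arm, the stage mix can differ between arms by chance even when arm sizes are identical. If stage is related to change in gait, an unadjusted comparison carries that difference into the estimate: an imbalance of 20 percentage points shifts the between-arm difference by 0.20 times the stage effect. Balancing on stage, adjusting for it, or both would remove most of this and could improve precision.

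**Working it through.** **Inputs.** From Sample size: predicted reductions in UPDRS III of 20.7 (SD 16.6), 7.9 (SD 6.3) and 2.6 (SD 2.2); two-sided alpha 0.05; power 90%; 66 before drop-out and 81 enrolled; drop-out 20%. From Concealment mechanism: three arms, 1:1:1. From Inclusion criteria: stages 2 and 3 eligible. The stage mix is not given, so 30% to 50% of patients in one stage is assumed.

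**1. Reproduce 66.** Take the first group against the second, with *n* per arm and a Welch *t* test.
- Difference: 20.7 − 7.9 = 12.8.
- Standard error at *n* = 22: √(16.6²/22 + 6.3²/22) = √(315.25/22) = 3.785.
- Noncentrality: 12.8/3.785 = 3.38, with 26.9 Welch degrees of freedom.
- Power is 90.3% at 22 per arm and 88.8% at 21 per arm. So 22 per arm is the smallest size that reaches 90%, and 3 × 22 = 66.
- Raising each arm by 20%: 22 × 1.2 = 26.4, rounded up to 27, and 3 × 27 = 81.

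A one-way ANOVA with a common SD of 16.6 also gives 22 per arm. Both routes assume equal arms.

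**2. Arm sizes if the sequence is unrestricted.** Arm counts are then multinomial (81; 1/3, 1/3, 1/3).
- P(exactly 27/27/27) = 81!/(27!)³ / 3⁸¹ = 1.0%.
- By simulation, the median gap between largest and smallest arm is 8, and P(gap ≥ 8) = 57%.
- P(some arm has fewer than 22 patients before any drop-out) = 28%.

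**3. Power cost**, first against second group, Welch test:

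| Total | Equal arms | Unrestricted, mean | Unrestricted, 5th percentile |
|---|---|---|---|
| 81 | 95.3% | 94.5% | 88.4% |
| 66 | 90.3% | 89.0% | 79.4% |

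The mean loss is 0.8 points at 81 and 1.3 points at 66.

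**4. Stage imbalance.** For two arms of 27, the SD of the difference in the proportion at one stage is √(2p(1−p)/27). This is 12.5 points at p = 0.3 and 13.6 points at p = 0.5. The simulated chance of a difference of 20 points or more is:

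| Share in one stage | Arm sizes | Some pair of the three arms | One given pair |
|---|---|---|---|
| 30% | fixed 27 each | 23.0% | 10.2% |
| 50% | fixed 27 each | 29.1% | 13.4% |
| 30% | unrestricted | 25.5% | 11.4% |
| 50% | unrestricted | 31.8% | 14.7% |

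Fixing the arm sizes lowers the chance by only about 3 points. Equal slip counts therefore settle steps 2 and 3 but not step 4.

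**The case against.** The strongest objection is that silence is being read as a method. Random numbers are also how permuted blocks or a shuffled list are made, and slips prepared in advance at 1:1:1 fit a fixed 27 per arm. The article condenses a fuller protocol, and details of blocks are commonly left there. This stands. A reader might infer that randomisation is plainly unrestricted and that unequal arms will follow, but the article does not say so. The arm-size figures are therefore conditional.

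Three other strong readings are also unsupported:

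- **Serious loss of power.** The mean loss is about one point. Only the lower tail is noticeable.
- **An invalid *t* test.** With SDs of 16.6 and 6.3, Student's *t* has a simulated false-positive rate of about 9% at 18 versus 26, when the smaller arm has the larger SD. The equally likely reverse, 26 versus 18, gives about 2.7%, and 22 versus 22 gives 5.4%. These SDs belong to UPDRS III, used as a stand-in for the gait outcome, and the plan tests homogeneity of variance first.
- **Early calendar stopping that leaves a fixed list unfinished.** The Recruitment and consent section says recruitment "will be completed on December 31, 2021, or after the required number is obtained, whichever comes first", but goes on to plan an extension request if numbers fall short.

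On stage, it is fair to say that no section shows stage 2 versus 3 to predict change in gait, that the two stages are adjacent, and that the error rate of a valid test already allows for chance imbalance. A SAP is also promised and may add covariates. This limits the importance of the point. It does not remove it, because the tests the article does name are unadjusted and adjustment costs almost nothing.

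**Conclusion.** The point holds in a limited form. The article names no restriction and no stratification factor, although its sample size rests on three equal arms of 22 and two severity stages are eligible. If the sequence is unrestricted, a gap of 8 or more patients between arms is more likely than not, but the consequence for power is small. Whether or not arm sizes are fixed, there is roughly a 23% to 32% chance that some pair of arms differs by 20 points or more in stage, and the named tests would leave that uncorrected.

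The stage figures rest on the assumed 30% to 50% mix and on the chosen 20-point threshold. For one given pair of arms the chance is about 10% to 15%. It would be too strong to call a large stage imbalance likely, or to call it bias: it is chance imbalance, and most trials run this way would not show a gap that large. Importance is minor to moderate.

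**What to change.** 1. **Analysis.** Include Hoehn-Yahr stage (2 versus 3) as a factor in the between-arm comparison of gait change, alongside treatment arm. Stage is already established at eligibility, so no new data are needed. The change can go into the SAP that the article says will be agreed before database lock and release of allocations.
2. **Allocation.** State in Sequence generation how 1:1:1 is enforced and whether stage is balanced. If the list is already balanced, one sentence is enough. If it is not, replace the list for envelopes not yet used with randomly permuted blocks of varying size (for example 3, 6 and 9), stratified by stage. Keep the block sizes from those who enrol.

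**Cost.** A new list, two envelope series and a short amendment; no extra patients or visits. Block ends become slightly more predictable in an open single-centre trial, which varying the block size limits. Recruitment is already under way and patients already allocated stay as they are, so the allocation change helps only the remainder. The adjusted analysis covers everyone.

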### Concealment mechanism

After signing the informed consent, participants will be randomly divided into the three aforementioned groups, at a ratio of 1:1:1. We will keep the allocation hidden during randomization. Slips of paper with treatment allocation will be placed in a sequentially numbered sealed opaque envelope and then opened in turn after obtaining informed consent. The research assistant will inform participants of their assigned study arm.

### Implementation

These procedures will be implemented in accordance with the protocol approved by the institutional review board (IRB). Implementation, monitoring, and incorporation of the protocol into the work arrangement will be performed by project managers. In addition, Academic Community’s Efforts to guidance will be also essential during this process.

### Blinding

The outcome assessor and data analyst will be blinded to the treatment allocation. Specifically, the assessor will enter data into a Microsoft Excel sheet, after completion of data collection, without knowledge of treatment group assignments. All entered data will be assigned corresponding codes and cleared of unnecessary information. Blinding will be broken after the data has been analyzed.

## Data collection and management

### Plans for assessment and collection of outcomes

All information shall be truthfully and accurately recorded in case report forms (CRF), at baseline and at 4 weeks after intervention. The evaluation of three-dimensional gait analysis and UPDRS will be conducted by a specially-trained evaluator, who is not clear about the trial group. The CRF and trial summary shall be submitted in time, at the end of the trial, to facilitate completion and accuracy of CRF examination.

### Plans to promote participant retention and complete follow-up

There are no specific plans to promote participant retention.

### Database management and quality control

Our research team will take effective measures to ensure the quality of research. Particularly, we will adopt the double entry method in order to ensure quality of data. The statistician will compare the two databases through the program, and in case of inconsistencies in the input results, he/she will check to identify the error. After final confirmation, the database will be saved and kept by a special person. Any future changes to the database shall be agreed upon, in writing, by the clinical study director, statistician, and data manager.

### Confidentiality

A specially assigned person will manage the relevant data during the trial period. All data will be identified using participants’ numbers, which will not directly display their personal information, to ensure confidentiality. Data will not be shared unless, explicitly approved by the researchers.

### Plans for collection, laboratory evaluation, and storage of biological specimens for genetic or molecular analysis during the trial period of for future use

None.

### Data access

Access to the data will be via contact to the corresponding author, upon signing of an agreement.

### Data analysis

All data analyses will be detailed in a Statistical Analysis Plan, to be agreed upon prior to database locking and release of intervention allocations. This will be after a thorough quality control check on all obtained datasets. Statisticians will use statistical product and service solutions (SPSS) or statistical analysis system (SAS) for statistical analyses, according to the intention-to-treat principle.

### Analysis of primary and secondary outcome measures

Analysis of categorical variables will be performed using the Pearson’s *χ*^2^ or Fisher’s exact tests, whereas continuous variables will be analyzed using a Student’s *t* test or appropriate non-parametric methods. All datasets will be analyzed at 95% confidence interval and will be tested by double-sided statistics. Data will be expressed as means ± standard deviation (SD). Data will first be tested for normality and homogeneity of variance prior to analysis, and if the normal distribution is satisfied, a *t* test will be used to compare 2 groups, whereas analysis of variance (ANOVA) with LSD or SNK methods will be used for multiple comparisons. Datasets that are not normally distributed will be analyzed using a rank sum test.

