### Outcome measures

Therapeutic evaluation will be carried out by the same team member who will be blinded to treatment allocation. The primary evaluation index of this study will be change of gait in PD patients, whereas the secondary evaluation indices will include evaluation of limb function, activity of daily life, and fall risk. We will adopt a three-dimensional gait analysis system for evaluation of gait information and surface electromyography for muscles related to lower limbs. We will employ the Unified Parkinson’s Disease Rating Scale (UPDRS) to assess the mental cognition, motor function, and daily living ability [22], while the Fall Efficacy Scale (FES) will be used to assess the risk of falls. Data across all measurements will be recorded in the data center [23].

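### Continuous outcomes are to be compared by unadjusted tests, with the compared quantity left open; adjusting for the baseline value would handle chance imbalance better and usually be more precise

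*Protocol article*

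**What the plan says.** The tests are fixed in the protocol article under *Analysis of primary and secondary outcome measures*:

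- For two groups: "if the normal distribution is satisfied, a *t* test will be used to compare 2 groups".
- For more than two groups: ANOVA "with LSD or SNK methods will be used for multiple comparisons".
- Otherwise: "Datasets that are not normally distributed will be analyzed using a rank sum test".

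No covariate is named. The section does not say whether the tests are applied to the change from baseline or to the value at 4 weeks.

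Three other places bear on this:

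- *Outcome measures*: "The primary evaluation index of this study will be change of gait in PD patients".
- *Plans for assessment and collection of outcomes*: data are "recorded in case report forms (CRF), at baseline and at 4 weeks after intervention".
- *Recruitment and consent*: patients who consent and "complete the baseline assessment will be randomized into the three groups". The baseline value is therefore a true pre-randomization covariate.

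*Sample size* is built on the reduction in UPDRS III, which is a change from baseline. *Data analysis* leaves further detail to a statistical analysis plan that is not shown.

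**The concern.** A t test, one-way ANOVA or rank sum test can take only one number per patient. That number must be either the 4-week value, which makes no use of the baseline, or the change, which subtracts the whole baseline as if the slope of the 4-week value on baseline were 1. When the true slope lies between 0 and 1, neither treats a chance baseline difference correctly.

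This matters more than usual here. The arms are small, and no stratification of the randomization is described. *Sample size* also states that no earlier three-dimensional gait results exist, so power on the actual primary outcome is unknown. Precision that can be had from data already collected is worth taking.

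**Working it through.** **Inputs from the protocol article.** Assumed UPDRS III reductions of 20.7 ± 16.6, 7.9 ± 6.3 and 2.6 ± 2.2; two-sided α 0.05; power 90%; 66 patients before and at least 81 after allowance for dropout; allocation 1:1:1. This gives 66/3 = 22 evaluable and 81/3 = 27 randomized per arm.

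**Assumptions, not in the article.** One correlation r between baseline and 4-week value in all arms, and equal SDs at both visits. I take r from 0.3 to 0.8.

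**1. The stated sample size.** For music exercise against exercise, the difference is 20.7 − 7.9 = 12.8 and the pooled SD is √[(16.6² + 6.3²)/2] = 12.55. A two-sample t test (noncentral t) has power 0.897 with 21 per arm and 0.910 with 22. So 22 per arm are needed, and 22 × 3 = 66, as stated. (An ANOVA with a common SD of 16.6 also gives 22 per arm, so the article's exact method cannot be inferred.) On either route the figure comes from an unadjusted comparison of changes.

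**2. Precision.** With the variance of the 4-week value set to 1, the variance factors are 1 for the 4-week value, 2(1 − r) for the change, and 1 − r² for ANCOVA. Relative to the change, ANCOVA is (1 − r²)/[2(1 − r)] = (1 + r)/2. Relative to the 4-week value it is 1 − r².

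| r | ANCOVA / change | ANCOVA / 4-week value |
|---|---|---|
| 0.3 | 0.65 | 0.91 |
| 0.5 | 0.75 | 0.75 |
| 0.7 | 0.85 | 0.51 |
| 0.8 | 0.90 | 0.36 |

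The reductions are therefore 25% at r = 0.5 against either alternative. At r = 0.7 they are 15% against the change and 49% against the 4-week value. A comparison with 90% power on change scores would have about 98%, 96%, 94% and 93% power with ANCOVA at r = 0.3, 0.5, 0.7 and 0.8.

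**3. Chance of imbalance.** In baseline SD units, the difference between two arm means has SD √(2/n).

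- n = 22: √(2/22) = 0.302, so P(|d| ≥ 0.5) = 2[1 − Φ(0.5/0.302)] = 0.097.
- n = 27: √(2/27) = 0.272, so P(|d| ≥ 0.5) = 2[1 − Φ(0.5/0.272)] = 0.066.
- At least one of the three pairs (range of three normal means): 0.22 at n = 22 and 0.16 at n = 27.

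**4. What an imbalance does.** Given a baseline difference d, the conditional bias is r·d for the 4-week value, (r − 1)·d for the change and 0 for ANCOVA with a common slope. For d = 0.5 SD:

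| r | 4-week value | change |
|---|---|---|
| 0.3 | +0.15 | −0.35 |
| 0.5 | +0.25 | −0.25 |
| 0.7 | +0.35 | −0.15 |
| 0.8 | +0.40 | −0.10 |

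**5. How firm the assumptions are.** With equal SDs, a change SD of s implies r = 1 − s²/(2·SD²). For an assumed SD of 10, the article's change SDs give r = −0.38, 0.80 and 0.98; for an assumed SD of 12 they give 0.04, 0.86 and 0.98. A single r does not fit the UPDRS III figures well, so the gains in step 2 illustrate the size and do not predict it.

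**The case against.** The strongest reply is that nothing here is invalid. Under randomization the unadjusted tests are unbiased on average, and their type I error is not inflated on this account. That stands. A reader might infer a broken analysis, and the article does not support that.

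A reader might also infer that the baseline is thrown away. The article does not support that either. The primary index is a change and the sample size uses a score reduction, so the likelier reading is a comparison of changes, which uses the baseline but over-corrects for it. The larger gains at high r (49% at r = 0.7) apply only if 4-week values are compared, which the article leaves open.

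It can be said that covariates belong to the unseen analysis plan. This stands only in part. The article is not silent: it names the tests, and a plan that used ANCOVA would replace them rather than fill them in.

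Finally, it would be too strong to say that adjustment can never lose precision. With three arms and one common slope, a pairwise contrast borrows a slope partly estimated from the third arm. With assumed slopes of 0.3, 0.7 and 0.98, the pooled slope is (0.3 + 0.7 + 0.98)/3 = 0.66. The best slope for the last two arms is (0.7 + 0.98)/2 = 0.84, which is slightly nearer to 1, the change score, than to 0.66. The loss in such a case is small, about 3% in variance in one worked illustration, and arm-specific slopes address it. The equal-SD and common-r assumptions are also strained by the article's own SDs, so the size of the gain stays uncertain.

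**Conclusion.** The concern holds as one of precision and of conditional bias, not of validity. The article commits to unadjusted tests and leaves open whether they compare changes or 4-week values. Either choice mishandles a chance baseline difference, in opposite directions, and either is generally less precise than adjustment.

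On the likelier reading (changes), the variance saving is 10% to 35% for r from 0.8 down to 0.3. This rests on equal SDs and a common r, and it will differ if these vary by arm. An imbalance large enough to matter is a realistic prospect: about one chance in five that some pair of arms differs by 0.5 SD or more at 22 per arm. The change should be made, but the trial's conclusions would not be invalid without it.

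**What to change.** - Make the primary analysis of each continuous outcome a linear model of the 4-week value on arm and the baseline value of the same measure, with robust standard errors. This also settles which quantity is analysed.
- If slopes may differ by arm, add arm-by-centred-baseline terms.
- Report adjusted arm differences with 95% confidence intervals.
- Keep the t test, ANOVA and rank sum test as supportive analyses, and say whether they are run on the change or on the 4-week value.
- Hoehn and Yahr stage (2 or 3) may be added as a prespecified covariate. This is optional, since the article gives no figure showing that it is prognostic for gait.

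The cost is analysis wording and a few degrees of freedom. No further data are needed, and the change can go into the statistical analysis plan, which the article says will be agreed before database lock and release of the allocations.
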